## 7.6. Sensitivity analyses

A first sensitivity analysis will be performed in the per-protocol population, defined as cases in which a valid FM-UE score could be assessed at 90 days post-stroke, in which at least eight cTBS sessions were performed, that were unaffected by a recurrent stroke and in which no major protocol violation was identified. A second sensitivity analysis will be performed on complete cases, without imputation of missing data. A third sensitivity analysis will be performed based on the intention-to-treat population, consisting of all randomized subjects (ITT2). In case of unbalanced baseline characteristics, additional sensitivity analyses may be performed that include the unbalanced baseline characteristic as a fixed effect in the generalized linear mixed model described in section 7.4.

## 7.7. Subgroup analyses

Predefined subgroup analyses will be based on baseline FM-UE extremity score (FM  $\leq$  20 versus FM  $>$  20); stroke subtype (ischemic stroke versus intracerebral haemorrhage); stroke location (cortical versus subcortical versus brainstem) and time to start of treatment (within 14 days versus 15 to 21 days). These analyses will be performed by including an interaction term between treatment and the previously described parameters in the linear regression model described in section 7.4.

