### 4.2 Inclusion criteria

To be eligible to participate in this study, a participant must meet all the following criteria:

- Age, 18 years or older
- First-ever unilateral ischemic stroke or intracerebral hemorrhage in a cerebral hemisphere or in the brainstem;
- Unilateral upper limb paresis with a motricity index between 9 and 99;
- Possibility to start cTBS treatment within 21 days after stroke onset;
- Signed informed consent.

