#### 4.4 Sample size calculation

The required sample size to test our hypothesis (superiority) in two groups is 440 subjects, based on a two-sided two-sample t-test power calculation with a minimal detectable effect of 6.6 points on the FM-UE scale (10% of the maximum score of 66, a mean score at 90 days of 42 and a standard deviation of 23 (calculated from the B-STARS trial data), a statistical significance level of 0.05 and statistical power of 0.85 (G\*power 3).

A study that specifically examined clinically important differences of FM-UE scores in stroke patients found that these ranged from 4.25 to 7.25 points, depending on the different facets of UE movement. A minimal clinically important difference of 6.6 points (10% of the maximum score FM-UE score) is in line with the module 'Noninvasive brain stimulation with rTMS' for the Dutch guideline 'Ischemic stroke and intracerebral hemorrhage'.

To compensate for possible loss to follow-up, we will include 454 patients. This sample size is also sufficient to demonstrate a treatment effect on secondary outcome measures. For example, for the ARAT, which tests upper limb-specific activity, a sample size of at least 396 would be required, based on a minimal clinically important difference of 5.7 and a mean score and standard deviation of 30 and 23, respectively (calculated from the B-STARS trial data), a statistical significance level of 0.05, and a statistical power of 0.8 (gigacalculator.com).

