### 3. Primary outcome

The primary outcome is the score on the Fugl-Meyer Upper Extremity Assessment (FM-UE) at 90 days post-stroke (Table 1). The FM-UE is a reliable and valid motor performance test consisting of 33 tasks that assesses upper limb motor impairment on a scale from 0 to 66 points, with a higher score indicating less impairment. The FM-UE will be assessed by certified assessors. Before

certification, assessors will receive on-site training by the team of coordinating investigators and must successfully complete an FM-UE exam.

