### 7.4. Primary analysis

The primary outcome is the FM-UE score at 90 days poststroke. The FM-UE reflects upper limb impairment on an ordinal scale from 0 (maximum impairment) to 66 points (no impairment).

The primary analysis is performed using a linear mixed model. Analysis will be performed in the primary estimand, including all randomized subjects who started at least 1 cTBS session. The outcome variable is the FM-UE score at 90 days poststroke. The model includes fixed effects for baseline FM-UE score; stratification factor (ability versus no ability to extend one or more fingers), age, gender, stroke subtype (ischemic stroke vs. intracerebral haemorrhage) and treatment (sham cTBS; active cTBS) and random effects for rehabilitation centre.

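### Effect modification by baseline FM-UE and by time to treatment is tested only on two-level splits, which costs power if the modification is graded

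*Combined protocol and SAP*

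**What the plan says.** SAP 7.7 opens its list with severity: "Predefined subgroup analyses will be based on baseline FM-UE extremity score", divided at 20 or below versus above 20. Stroke subtype and stroke location follow, and the list ends with "time to start of treatment (within 14 days versus 15 to 21 days". The method is stated in one sentence: "These analyses will be performed by including an interaction term between treatment and the previously described parameters", within the model of SAP 7.4. Protocol 10.2 gives the same four factors and the same cuts.

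In SAP 7.4 the severity score is not grouped: "The model includes fixed effects for baseline FM-UE score". SAP section 3 describes the FM-UE as a test that "assesses upper limb motor impairment on a scale from 0 to 66 points". For timing, protocol 4.2 sets the upper limit: "Possibility to start cTBS treatment within 21 days after stroke onset". Protocol 8.1.3 records the date of stroke onset, protocol 8.3 records the date and time of each session, and SAP 7.2 already lists the interval from onset to first cTBS as a baseline variable.

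Neither document plans a continuous interaction for these two factors, explains either cut-point, or gives the expected baseline distribution of either variable.

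**The concern.** Interaction tests have much less power than the test of the main effect. Splitting a measured variable lowers that power further when the effect changes gradually. With the day-14 cut, a patient starting on day 14 is treated as identical to one starting on day 5 and as different from one starting on day 15.

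Timing matters to the trial's rationale. Protocol 13.1 cites a mean FM-UE difference of 9.3 points when treatment starts within the first month, against 1.14 points later, and argues for an early start. If benefit does fall off gradually with delay, or changes with severity, the planned tests are more likely than necessary to end in a report of no difference between subgroups.

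Only two of the four factors are concerned. Stroke subtype and stroke location are categorical by nature.

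**Working it through.** **1. The plan's own figure.** Protocol 4.4 is "based on a two-sided two-sample t-test power calculation" with a difference of 6.6, SD 23, two-sided alpha 0.05 and power 0.85. The normal formula gives n per arm = 2 × (1.960 + 1.036)² × 23² / 6.6² = 218.1, so 219. The exact t-test gives 219.03, so 220 per arm and 440 in total, as stated. The documents give no power or information figure for the subgroup interactions.

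**2. Information retained by a split.** For a linear treatment-by-covariate interaction, the fraction retained R is the squared correlation between the covariate and its two-group indicator:

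R = p(1 − p) × (difference between the two group means)² / variance of the covariate,

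where p is the share at or below the cut. For a normal covariate this becomes φ(z_p)² / [p(1 − p)].

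*FM-UE spread evenly over 0 to 66, cut at 20.* p = 21/67 = 0.313, group means 10 and 43.5, variance 374. R = 0.215 × 33.5² / 374 = 0.646, a loss of 35%.

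*Days spread evenly over 7 to 21, cut at 14.* p = 8/15 = 0.533, group means 10.5 and 18, variance 18.67. R = 0.249 × 7.5² / 18.67 = 0.75, a loss of 25%.

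**3. Range over assumed distributions.** All of these are assumptions.

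| Variable and assumed shape | Loss |
|---|---|
| Any normal variable, cut at the median | 36% |
| Any normal variable, 25/75 split | 46% |
| FM-UE, U-shaped | 24–27% |
| FM-UE, skewed low | 27–30% |
| FM-UE, uniform 0–66 | 35% |
| FM-UE, normal (25, 20) / (30, 20) / (35, 18) | 38% / 42% / 49% |
| Days, uniform from day 3–10 to day 21 | 25–30% |
| Days, frequency rising to day 21 | 28–39% |
| Days, normal (14, 4) | 30–35% |
| Days, normal (16, 3) | 37–38% |
| Days, normal (17, 3) | 43–44% |

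The overall range is about 24% to 49%. A split more uneven than about 80/20 could lose more than half.

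**4. Conversion to power.** For an interaction with 80% power on the continuous scale, power after the split = Φ(2.80 × √R − 1.96).

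- R = 0.75: Φ(0.466) = 68%, equivalent to 330 of 440 patients.
- R = 0.637: Φ(0.276) = 61%, equivalent to 280.
- R = 0.539: Φ(0.097) = 54%, equivalent to 237.
- R = 0.509: Φ(0.039) = 52%, equivalent to 224.

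**5. Simulation check.** 3,000 trials of 440 patients were simulated for each case, with the linear main effect of the covariate kept in the model. Power on the continuous scale was 79–80%. After the split it was 61% (FM-UE uniform), 66% (U-shaped), 65% (skewed low), 68% (days uniform 7–21) and 55% (days normal (17, 3)).

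**6. Context.** With an even split, N = 440 and SD 23, the standard error of the difference between subgroup effects is 4 × 23 / √440 = 4.39. The difference detectable with 80% power is 2.80 × 4.39 = 12.3 points, or about 8.8 if baseline covariates correlate 0.7 with the outcome (an assumption). The trial's target effect is 6.6.

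**The case against.** **The loss depends on shape, and the argument runs both ways.** R is a squared correlation, so it is symmetric. If the true modification is a step at the cut, the split loses nothing and a linear test loses the same fraction. FM-UE is bounded and may have floor or ceiling effects. For a symmetric inverted U over a uniform 0–66 baseline, a linear interaction captures none of the modification and the cut at 20 about 15%. The figures in protocol 13.1 compare the first month with later periods and do not show a gradient within 21 days. All this stands: the loss must be stated as conditional on linearity, and a linear term alone is not enough.

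**The cut-offs cannot check linearity.** Two subgroup estimates always fit a straight line. This also stands, and it is why the fix needs a flexible term.

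**The practical gain is limited.** For a 6.6-point difference between even halves, unadjusted, power is Φ(6.6/4.39 − 1.96) = 32% with the split. For the equivalent linear gradient in a normal variable it is Φ(1.503/√0.637 − 1.96) = 47%. Either test would often be inconclusive. This is correct, and it makes the change an improvement rather than a necessary correction. Prespecified cut-points with an interaction test are a defensible choice.

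**An inference to avoid.** A reader might note that the "stratification factor (ability versus no ability to extend one or more fingers") is absent from the subgroup list and count that as part of the same error. The documents do not support this. The factor is binary, so nothing is discarded, and SAP 7.4 adjusts for it. Testing it as a modifier would be a separate, optional fifth interaction.

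**Conclusion.** The point holds in a conditional form. For baseline FM-UE and time to treatment, the only planned interaction tests use two-level splits, although continuous values are available for both. If modification is roughly linear, the split loses about 24% to 49% of the information on that interaction. A test with 80% power on the continuous scale then has about 54% to 68% in the simulated and generic cases, and about 52% at the 49% extreme.

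A reader might take this to mean that the plan is known to discard a quarter to a half of what the trial can learn about who benefits. The documents do not support that. They give no baseline distribution for either variable and no evidence that modification is linear, and two of the four factors are unaffected. Nor do the primary analysis or the figures of 440 and 454 depend on this point. It is a low-cost improvement to a secondary part of the analysis.

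**What to change.** In SAP 7.7:

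- Make treatment × continuous baseline FM-UE and treatment × days from stroke onset to first session the interaction tests for these two factors.
- Add days as a main effect in the timing model, because it is not in the SAP 7.4 model. Baseline FM-UE is already there.
- Add a restricted cubic spline, or a similar flexible term, as the prespecified check on linearity.
- Keep the cuts at FM-UE 20 and day 14 for displaying subgroup estimates, and say that this is their purpose.
- Align protocol 10.2 or refer it to the SAP.

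No new data are needed. The SAP has been revised before on reviewer recommendations (SAP section 8), and SAP 5.1 keeps allocation concealed until database lock, so the change can be made blind. The cost is reliance on a linear shape for the main interaction test, which the spline examines, and slightly more analysis and reporting.

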## 7.8. Safety

We will report (serious) adverse events tabulated per treatment group.

## 8. Change log

| Version | Changes                                                                                                                                                                                                                                                                                                                                                                                                                                             | Date       |
|---------|-----------------------------------------------------------------------------------------------------------------------------------------------------------------------------------------------------------------------------------------------------------------------------------------------------------------------------------------------------------------------------------------------------------------------------------------------------|------------|
| 2       | 

- Section added on blinding and data lock

- Additional sensitivity analyses (complete case and ITT2) added

                                                                                                                                                                                                                                                                                  | 14-10-2024 |
| 3       | Based on reviewer recommendations: 

- Gender added as fixed effect in primary and secondary analyses

- Per protocol population definition adjusted to: ‘cases in which a valid FM-UE score could assessed at 90 days post-stroke, in which at least eight cTBS sessions were performed, that were unaffected by a recurrent stroke and in which no major protocol violation was identified.’

 | 16-05-2024 |

## 1. Objectives

### 1.1. Efficacy objective

To assess whether 10 sessions of cTBS of the contralesional primary motor cortex (M1) combined with regular care upper limb training, started within three weeks after stroke onset and continued every working day for two weeks, reduces upper limb impairment at 90 days after stroke, compared to sham stimulation.

### 1.2. Health-economic objective

We will perform a cost-utility analysis from a societal perspective to assess whether 10 sessions of cTBS are cost-effective compared to sham cTBS in promoting upper limb recovery after stroke.

## 2. PICOTS

### 2.1. Patients

The patient population consists of patients with ischaemic stroke or intracerebral haemorrhage with unilateral upper limb impairment who are enrolled in a clinical rehabilitation programme in The Netherlands.

### 2.2. Intervention

The intervention consists of ten daily sessions of cTBS, delivered over the contralesional primary motor cortex, started within 21 days post-stroke. The intervention will be delivered by a physical or occupational therapist immediately before regular care upper limb therapy. A cTBS session consists of localization of the treatment target, determination of the treatment dose, and the actual stimulation paradigm. The intervention is intended to modulate neuronal activity in the motor cortex, to facilitate the effect of subsequent upper limb therapy.

## 2.3. Comparison

The cTBS intervention is an addition to regular care. The comparison consists of ten daily sessions of sham cTBS. Sham cTBS is delivered under the same conditions but using a sham TMS coil that does not produce effective stimulation. Sham cTBS is required to rule out a potential placebo effect induced by TMS.

## 2.4. Outcomes

### **Cost-effectiveness**

The main outcome of this health economic evaluation is the integration of incremental costs and incremental quality adjusted life years (QALYs) of cTBS compared to usual care.

### **Costs**

The costs of the intervention are subdivided into direct medical costs, costs for patients and families, and productivity costs. Medical costs include the costs of the intervention/procedure itself, costs of clinical and outpatient rehabilitation and other medical costs, such as hospitalizations or first-line physical therapy. These costs are described in section 6.1 to 6.3. Informal care and productivity costs are described in section 6.4.

### **Effects**

The effects will be determined based on quality-adjusted life years (QALYs), combining quality of life with mortality data and are described in section 5.

## 2.5. Time

On average, stroke patients spend 8 to 12 weeks in clinical rehabilitation and recover around 70% of lost function within the first 3 months after stroke. Subsequently, patients spend an average of 3 months in outpatient rehabilitation. Thereafter, patients reintegrate into society and if applicable, reintegrate into the workforce. We will extrapolate the quality of life and costs at one-year post-stroke over longer periods of time to investigate the potential impact on long-term cost-effectiveness. At one-year post-stroke, most patients

have completed rehabilitation and recovery will have plateaued. Therefore, we will perform a scenario analysis with a time horizon of the cost-utility analysis of one year after stroke.

## 2.6. Setting

The intervention will be implemented in medical specialist rehabilitation centres. Health care professionals within these centres are not familiar with cTBS treatment, but are familiar with other medical devices, such as electrical stimulation. The iMTA questionnaires are adapted to the patient population to make sure that the reported data is applicable and relevant for the investigated setting.

## 3. Study design

B-STARS2 is a multi-centre, double-blind, randomized, sham-controlled, clinical trial. Participants will be recruited from 16 rehabilitation centres in the Netherlands over a period of 51 months (Q2 of 2024 to Q4 of 2028). The total duration of follow-up for each participant is until one year after stroke. The total study duration is 63 months.

The intervention consists of ten daily sessions of active or sham cTBS, delivered over the contralesional primary motor cortex, started within 21 days post-stroke and combined with regular care upper limb therapy.

The cost-utility analysis will be performed alongside the B-STARS2 trial. During the trial, data on patient-reported medical consumption and productivity losses will be acquired through digital questionnaires at 6- and 12-months post-stroke and quality of life will be assessed at 3- and 12-months post-stroke (Figure 1).

[figure not shown]

**Figure 1.** Study timeline.

## 4. Cost-utility analysis

### 4.1. Primary analysis

We will perform a cost-utility analysis from a societal perspective comparing active cTBS to sham cTBS. We will collect data on procedural costs, other direct medical costs, indirect costs, and patient-level quality of life. Missing data will be imputed with multiple imputation and the uncertainty of the economic evaluation will be assessed with bootstrapping techniques.

To be able to extrapolate trial findings and to perform other scenario analysis, a decision-analytical model (a decision tree) will be developed. In this decision tree, we will correlate EQ-5D-5L outcomes and costs to Fugl-Meyer Upper Extremity outcomes.

### 4.2. Scenario analyses

We will perform several scenario analyses. In the first scenario analysis, we will analyze the effects up to one-year post-stroke to investigate the impact on short-term cost-effectiveness. In a second scenario analysis we will investigate the potential impact of

sham cTBS on the cost-effectiveness analysis, as sham cTBS may have a placebo effect that complicates a comparison against the usual care situation. In a third scenario analysis, we will estimate cost-effectiveness if we exclude neuronavigation costs from the total costs of the intervention, because neuronavigation is only required for research purposes. A double-blind sham-controlled design requires blinding of the TMS therapist and the patient to the TMS coil used for treatment. Therefore, a separate coil is used to determine the treatment location and dose. Navigation is required to navigate the active or sham TMS coil to the target location without using stimuli. In a standard care situation, the same coil can be used for dose and location determination and treatment, eliminating the need for navigation.

## 5. Budget Impact Analysis

We will extrapolate the results from the cost utility analysis to all stroke patients who are eligible for the intervention. The budget impact analysis will be performed according to the Dutch BIA guideline and using the ZonMw calculation tool. The BIA will be performed in a probabilistic way and will take a 1) net budgetary framework healthcare (BKZ) perspective and a 2) health insurance / third party payer perspective.

## 6. Effects

Quality of life will be assessed with the EQ-5D-5L, within 3 weeks after stroke and at 3-, 6- and 12-months post-stroke. Quality of life is assessed at 3 and 6 months post-stroke, when most patients will have completed clinical rehabilitation. Quality of life will be assessed again at one-year post-stroke, when recovery has plateaued, and most patients will have ceased rehabilitation and reintegrated into society. Quality of life is assumed to increase logarithmically between stroke onset and 12 months post-stroke based on existing data from our phase II RCT, B-STARS. QALYs will be assessed by combining mortality and quality of life using an area-under-the-curve approach. The Dutch tariffs will be used to convert the EQ-5D-5L scores into a utility score. This utility score ranges from 0 to 1, in which 0 corresponds to death and 1 corresponds to perfect health.

## 7. Costs

### 7.1. Costs of the intervention

Costs of the intervention/procedure itself will be calculated with a bottom-up approach estimated with a mixed method approach. For instance, we will use financial information from the rehabilitation centres combined with estimates on the time spent by personnel on the interventional procedure. The estimate will include the following costs: purchase and maintenance of the equipment, direct and indirect costs of personnel and costs of facilities.

### 7.2. Clinical and outpatient rehabilitation costs

Other healthcare resource use will be assessed in two ways. Direct healthcare costs during clinical rehabilitation will be calculated by multiplying the length of stay of the patient and the estimated daily cost of clinical rehabilitation for that rehabilitation centre. Similarly, outpatient rehabilitation costs will be calculated by multiplying the duration of the patient's outpatient rehabilitation with the estimated daily costs of outpatient rehabilitation for that rehabilitation centre. The costs of outpatient rehabilitation are only available for patients who go to the same rehabilitation centre for clinical and outpatient rehabilitation. Missing data will be imputed.

